### Intervention arm

The Akwenda CP programme comprises five elements (see figure 2, online supplemental tables 1 and 2 for detailed description):

**Figure 2 F2:**
[figure not shown]
Timetable for delivering the intervention through the five components over a period of 11 months. CP, cerebral palsy; GAS, Goal Attainment Scale; CVI, Cerebral Visual Impairment; TAD, Technical Assistive Device.

#### Caregiver-led training workshops

The core is a series of seven workshops for caregivers of children with CP. This workshop series is based on the Malamulele Onward Carer-2-Carer Training Programme (MOC2CTP).^38 39^ Four caregivers of children with CP from Iganga have been identified and trained to lead the workshops following the detailed MOC2CTP manual (see figure 2 and online supplemental table 1).

#### Therapist-led practical group sessions and workshops

Trained paediatric occupational and physiotherapists will run monthly practical sessions for groups of caregivers, based on the material covered in the caregiver-led workshops. The emphasis of the practical sessions is on active caregiver participation and includes training caregivers to facilitate their children’s active participation and engagement. The sessions will be structured such that the therapist will be able to give each child individual attention during group activities. The parent facilitators will assist the therapists during these practical sessions. The therapists will in addition run four workshops including (1) technical assistive devices (TADs); (2) goal-based training; (3) nutrition and (4) epilepsy (see figure 2 and online supplemental table 2). To ensure consistency and quality, a therapist manual was developed for the intervention.

#### Provision of TADs

TADs are an important part of evidence-based rehabilitation, promoting greater independence and enabling children to perform tasks they were formerly unable to accomplish within mobility, self-care, eating and communication domains.^40^ Each child’s need for TAD will be assessed by therapists at baseline, and the children and caregivers will be involved in deciding what TAD they need. Examples are wheelchairs, standing frames, posture support chairs, walking devices, parallel bars, communication boards and cut-out feeding cups. When possible, TAD will be locally manufactured with affordable local materials, and caregivers will be involved in cost-sharing to ensure affordability and sustainability.

#### Goal-directed training

Goal-directed training is a child-active, motor learning approach.^41^ Several studies have demonstrated successful goal-directed programmes in HICs,^42–45^ while there are no reports from LMICs. The child and caregiver, supported by a therapist, will identify three realistic goals and create action plans for how to achieve them through daily training and practise in the home environment. The goal-setting procedure will start during the fourth month. By this time, the therapist has become acquainted with the child, and the caregiver has attended the caregiver-led workshops and hence will have a more realistic understanding of the child’s potential. Children-issued TAD will have a fourth goal relating to their use.

#### Communication and advocacy for behavioural and social change

The communication and advocacy (C&A) component will address stigma, discrimination and exclusion of children with disabilities, and is based on Communication for Development, a systematic and evidence-based strategy to promote positive social and behavioural changes.^46^ The broad themes for C&A are human rights of children with disabilities and barriers to services and how to overcome them. C&A will be run by a community social worker using community meetings and radio talk shows. Community meetings will involve political and religious leaders, teachers and health workers. Caregivers and community stakeholders will participate in a joint meeting to develop a community action plan for how to make services more inclusive.

### Standard care arm

Standard or usual care refers to that available for children with CP in the study area. Currently, children have access to primary healthcare and the local hospital. Support and services are rare in this rural setting with no specialised services at the local public hospitals or health centres. There are some private actors and non-governmental organisations working in the surrounding area, which may provide occasional sessions of physiotherapy or occupational therapy, and unpredictable donations of TADs such as wheelchairs or crutches.^4^ Caregivers in the usual care group will be asked to keep a monthly care diary during the waiting period.

### Sample size

From the initial cohort of 97 children with CP, 82 children had survived.^36^ In order to include younger children, we have identified 20 additional children with CP living in the area. From these two samples, 88 children will be recruited to form two comparable groups each with 44 children. In addition, the primary caregiver of each child will be included in the two arms, and 40 community representatives will be included in the intervention arm for evaluation of the C&A component.

To explore whether this sample size was sufficient for detecting a true effect of the intervention, we did power calculations to determine what mean difference in Pediatric Quality of Life Inventory (Peds-QL; primary outcome measure for caregivers) scores was needed between arms. We used a Peds-QL mean of 12.5 and SD of 18.6, from a previous study in Ghana on caregivers of children with CP.^22^ In our population with 44 per group allowing for a 10% non-participation at follow-up, a mean difference of at least 12.5 points between groups is needed for 80% power and a type I error of 0.05. Considering that the mean improvement after a parent training intervention in Ghana in Peds-QL was +31.3 (95% CI 25.6 to 37.0), this seems plausible.^22^

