## Methods

### Study design

The project is designed as a quasi-randomised controlled clinical study conducted according to the Standard Protocol Items: Recommendations for Interventional Trials guidelines (see figure 1). Children with confirmed diagnoses of CP will be assigned to either a study group or control group, based on geographical regions. The study group will receive the Akwenda CP programme during the first year, while the control group will be on a waitlist and receive usual care. The control group will receive the intervention after 1 year. Children and caregivers of the first intervention group will be encouraged to continue with the parent-led workshops and to implement new caregiving skills and behaviours during the second year. Both groups will be assessed prior to the start of the intervention, after 1 year and after 2 years.

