### Participants and recruitment

Participants will be from a population-based cohort of children with CP identified from previous screening carried out at IM-HDSS in 2015 using the definition of CP Surveillance in Europe.^25 37^ In addition, children with CP aged 2–6 years living in the same area will be recruited by the community development officer. The CP diagnosis will be confirmed by a child neurologist using the same definitions. Hence, the study population will be between 2 and 23 years at the onset of the intervention study.

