#### Data management and analysis

Data will be collected in Open Data Kit using tablets, and electronic data will be managed through a secure database. The use of electronic data collection with built-in quality control will minimise missing or inaccurately entered data. The researchers will supervise data collection and monitor the database in real time to address any quality issues that might be arising. Data will be analysed using Stata version 14.2. Standard analysis methods for a randomised controlled trial, including general linear mixed models, will be used to make comparisons between the intervention group and the waitlist group on an intention-to-treat basis. Effect estimate will be presented as a mean difference and 95% CI. Secondary outcome analyses will use similar methods to compare all other outcomes between groups immediately post-intervention and again 1 year later. The GAS goal attainment scores for the intervention group will be analysed with paired t-tests on a within-group basis. A senior statistician will guide and assist with the analysis.

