### Patient and public involvement

The Akwenda CP programme and the study design have been developed in collaboration with caregivers, community leaders and local health professionals. All of these stakeholders were invited to a dissemination event in January 2019 where the results from the first screening study from 2015 were reported. At the same time, plans for a 4-year follow-up study and this intervention study were presented and discussed. Local therapists and social workers from the region, together with four caregivers, have thereafter participated in the development and adaptation of the intervention programme (see online supplemental file 1), and in designing and planning the study. The parent-led workshop series, a core part of the intervention programme, was developed and refined by a team of therapists and the parents of children with CP in South Africa.

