#### Safety

As the study is not a drug trial, there is no Data Safety Monitoring Committee. A COVID-19 risk management protocol has been developed and approved by the Higher Degrees Research and Ethics Committee, School of Public Health, College of Health Sciences, Makerere University and will be strictly adhered to. Any adverse events associated with the study will be screened weekly by the treating therapists, and reported to the PI, and referred to the Ethics Committee if considered serious. Any decision to describe interim results or terminate the trial will be made by the investigators with oversight from the Ethics Committee.

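### The adverse-event rule does not ensure that deaths are recorded, reported and ascertained equally in both arms, although the cohort's own survival makes several deaths likely

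*Protocol article*

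**What the plan says.** **Survival.** The Sample size section of the Protocol article reports: "From the initial cohort of 97 children with CP, 82 children had survived". It gives no date for that count. The cohort was "identified from previous screening carried out at IM-HDSS in 2015" (Participants and recruitment). The Patient and public involvement section says that at an event in January 2019 "plans for a 4-year follow-up study and this intervention study were presented and discussed".

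**Trial population.** To bring in younger children, "we have identified 20 additional children with CP living in the area". From both sources, "88 children will be recruited to form two comparable groups each with 44 children" (Sample size).

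**Follow-up.** "Both groups will be assessed prior to the start of the intervention, after 1 year and after 2 years" (Study design). The control group is on a waitlist with usual care for the first year and then receives the programme. Under Standard care arm, its caregivers are asked to keep a monthly care diary while they wait.

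**Safety rule.** The Safety section covers adverse events that are associated with the study. The treating therapists screen for them weekly, and they are "reported to the PI, and referred to the Ethics Committee if considered serious". The same section says there is no Data Safety Monitoring Committee.

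**Outcomes.** None of the child, caregiver or community measures listed is death or vital status.

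**The concern.** Association with the study is the entry condition of the safety rule. Seriousness is considered only for events that have already met it. A death not thought to be linked to the programme therefore need not reach the PI or the Ethics Committee under this text.

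The screening is also tied to the people who deliver treatment. During year 1, the only year with a usual-care comparator, just one arm has such people. Deaths could therefore be picked up by different routes and with different completeness in the two arms.

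This matters because the cohort has already lost about one child in seven. Where background mortality is of that order, single deaths are hard to attribute, and the useful safety information is the count from all causes, collected in the same way in each arm. The programme includes nutrition and epilepsy workshops, feeding and posture devices and group sessions, so readers will ask how many children died in each arm.

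**Working it through.** **Step 1: the rule applied to a death in year 1.**

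| | Intervention arm | Waitlist arm |
|---|---|---|
| Weekly screening by treating therapists | Yes | No treating therapists while on usual care |
| Condition for entering the reporting chain | Linked to the study | The same, although the programme has not been received |
| Other contact described between assessments | Programme sessions | Monthly care diary kept by the caregiver |
| Assessment at 1 year | Yes | Yes |
| Data Safety Monitoring Committee | None | None |

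Only the year-1 assessment is the same route in both arms. A missed assessment shows that a child was not seen. It does not by itself give the date or cause of a death, and the Safety section attaches no report to it.

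**Step 2: expected number of deaths.** The article states no expected number, so there is none to reproduce. Its one computed design figure, the detectable PedsQL difference, plays no part here.

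Inputs:
- Cohort 97, alive 82 (Sample size): deaths 97 − 82 = 15, and 15/97 = 15.5%, exact 95% interval 8.9% to 24.2%.
- Interval T = 4 years. This is inferred from the 2015 screening and the mention of a 4-year follow-up study. T = 3, 5 and 6 are shown as alternatives.
- N = 88, 44 per arm (Sample size).
- Time at risk t = 1 year for the comparison with usual care, and t = 2 years for the whole trial (Study design).

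Formula, assuming a constant hazard and the same risk in all 88 children: expected deaths = N × [1 − (82/97)^(t/T)].

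With T = 4:
- Year 1: (82/97)^(1/4) = 0.959, a risk of 4.1%. 88 × 0.0411 = 3.6 deaths, or 1.8 per arm.
- Two years: (82/97)^(1/2) = 0.919, a risk of 8.1%. 88 × 0.0806 = 7.1 deaths, or 3.5 per arm.
- Chance of at least one death in year 1: 1 − (1 − 0.0411)^88 = 97.5%.

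**Step 3: sensitivity.**

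| Assumption | Deaths in year 1 | Deaths over 2 years |
|---|---|---|
| T = 3 years | 4.8 | 9.3 |
| T = 4 years | 3.6 | 7.1 |
| T = 5 years | 2.9 | 5.7 |
| T = 6 years | 2.4 | 4.8 |
| T = 4, lower limit of 15/97 | 2.0 | 4.0 |
| T = 4, upper limit of 15/97 | 5.9 | 11.4 |

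Under each of these assumptions, at least two deaths are expected in the controlled year and at least four over two years.

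**The case against.** The strongest reply is that this is a condensed article. Death forms, adverse-event definitions and participant-flow reporting commonly sit in the full protocol, which is not shown. Nothing in the article says that deaths will be left out. Several features point towards ascertainment: the same cohort's deaths were counted before, the study runs inside a demographic surveillance site, both groups are assessed at 1 and 2 years, waitlist caregivers keep diaries, and the database is monitored in real time.

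Much of this stands. A reader might infer that deaths would not be counted by arm at all. The article does not support that, because a death would surface as a missed assessment of an identified child in a known arm. Nor does the absence of mortality from the outcome list amount to an error in a rehabilitation trial. What remains is that the Safety section states a rule rather than leaving a gap, and following it exactly gives filtered and unequal recording.

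A reader might also infer that the programme's own staff would usually put deaths down to the underlying condition. The article does not say who judges association and gives no causes of death, so that is conjecture. The same holds for bias in the score comparisons among survivors. The article promises that its models "will be used to make comparisons between the intervention group and the waitlist group on an intention-to-treat basis", and the handling of scores after death may properly be left to the analysis plan. No size can be put on such a bias from the documents.

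Finally, about 7 deaths is not the number in the comparison with usual care. The control group receives the programme after 1 year, so about half of those deaths would fall after both arms had been offered it. With about 1.8 expected deaths per arm in the controlled year, all-cause counts cannot establish balance or imbalance. They can only show what happened.

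**Conclusion.** The point holds in a limited form. The adverse-event rule as published does not ensure that deaths are recorded and reported, or that they are ascertained in the same way in both arms. Several deaths are nevertheless likely: about 3.6 among 88 children in the controlled year and about 7 over two years, with a range of roughly 4 to 11 over two years from the uncertainty in 15/97.

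These figures rest on a 4-year interval that the Sample size section does not state, on a constant hazard in children who had already survived the earlier period, and on equal risk in the 20 added younger children, for whom no mortality figure is given. The conclusion does not depend on the exact number, since intervals of 5 or 6 years still give 5.7 or 4.8 deaths over two years. This is an inexpensive improvement to safety oversight and to even-handed ascertainment. It does not show that the trial would lose sight of its deaths or that its main results would be biased.

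**What to change.** Amend the Safety section to say that every death in either arm, from baseline to year 2, is recorded with its date and, if known, its cause, and is reported to the PI and the Ethics Committee regardless of presumed association with the study.

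State that vital status at years 1 and 2 is obtained by the same procedure in both arms, from the family contacts already planned and the surveillance site. Report all-cause deaths by arm descriptively, with the controlled year shown separately from the year after the waitlist group starts the programme.

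The change is one of protocol wording, with approval of the amendment by the Research and Ethics Committee. It uses contacts and a surveillance system that already exist. The downside is a few more reports to the Ethics Committee. No formal mortality comparison should be promised, because the counts will be too small for one.

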### Randomisation and blinding

Since the community and advocacy intervention will target the community, all children from a particular village need to be in the same group. Children will thus be allocated to groups depending on the village where they reside. Neighbouring villages will be clustered together to reduce contamination between groups resulting in two geographically defined groups, which will be matched for age, sex and motor function. The decision regarding which group will receive the intervention first will be decided by a coin flip. A team of therapists and a social worker will administer the assessments and surveys before the study to capture background and baseline data. A group of independent therapists, not involved in the intervention, will administer the outcome measures after the interventions. These examiners will be blinded to group allocation.

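### The detectable difference of 12.5 points does not follow from its stated inputs, which give 11.7 to 11.9, and the calculation makes no allowance for allocating whole villages in two areas

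*Protocol article*

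**What the plan says.** The Sample size section of the protocol article fixes the number from the available cohort: "88 children will be recruited to form two comparable groups each with 44 children". It then asks what this number can detect on the primary caregiver outcome. The inputs are printed: "We used a Peds-QL mean of 12.5 and SD of 18.6, from a previous study in Ghana on caregivers of children with CP". The analysed number is described as follows: "In our population with 44 per group allowing for a 10% non-participation at follow-up". The result is that "a mean difference of at least 12.5 points between groups is needed for 80% power and a type I error of 0.05". Support for the target comes from one sentence: "Considering that the mean improvement after a parent training intervention in Ghana in Peds-QL was +31.3 (95% CI 25.6 to 37.0), this seems plausible".

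The Randomisation and blinding section describes the allocation: "Children will thus be allocated to groups depending on the village where they reside". Neighbouring villages are merged into two geographic groups matched on age, sex and motor function, and one coin flip decides which group is treated first. The Sample size section gives no ICC, design effect or number of clusters.

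**The concern.** A printed result should follow from the inputs printed beside it, and this one does not. The inputs also describe caregivers as if they had been allocated one by one, whereas the design allocates villages in two blocks. Finally, a required difference between arms is called plausible by reference to a figure that the text words as a change after an intervention. Such a change can include time trend, regression to the mean and response bias.

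This is the only power statement in the article, and it is offered to show that the sample is sufficient. Readers will judge the caregiver result, positive or null, against a claim of 80% power for 12.5 points. That claim is slightly too pessimistic for independent data. It may be too optimistic for the design as described.

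**Working it through.** **Inputs from the Sample size section.** SD 18.6; 44 per group; 10% loss, so 44 × 0.9 = 39.6 analysed per group (39 to 40 in whole numbers); power 80%; type I error 0.05. Sidedness is not stated, and two-sided is assumed.

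**Step 1: reproduce the plan's figure.** Detectable difference = (z for 1 − α/2 + z for power) × SD × √(2/n).

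- Normal approximation: (1.960 + 0.842) × 18.6 × √(2/39.6) = 11.71.
- Noncentral t: 11.86.
- With 40 or 39 analysed: 11.65 to 11.80 (normal) and 11.80 to 11.95 (t).

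The printed 12.5 is not reproduced. Nearby readings do not reach it either:

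| Variant | Normal | t |
|---|---|---|
| 44 per group, no loss | 11.11 | 11.24 |
| 39.6 per group, one-sided | 10.39 | 10.49 |
| 39.6 per group, 90% power | 13.55 | 13.72 |

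**Step 2: work back from 12.5.** At 80% power, 12.5 points needs 35 (normal) or 36 (t) analysed per group. That is 39 or 40 recruited after 10% loss, not 44. With 39.6 analysed, power for 12.5 is 84.9% (normal) or 84.0% (t).

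**Step 3: how much clustering the slack covers.** The detectable difference grows with the square root of the design effect (DE), so 12.5 absorbs (12.5/11.71)² = 1.14 (normal) or (12.5/11.86)² = 1.11 (t).

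**Step 4: villages as the clusters.** DE = 1 + (m − 1) × ICC, with m the mean number analysed per village. The protocol gives neither an ICC nor the number of villages contributing participants. Assumed here: ICC 0.05 to 0.10 and 20 to 40 villages. With 79.2 analysed in total:

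- 40 villages, ICC 0.05: m = 79.2/40 = 1.98; DE = 1.049; detectable difference 11.71 × √1.049 = 12.0 (normal) or 12.1 (t).
- 20 villages, ICC 0.10: m = 79.2/20 = 3.96; DE = 1.296; 11.71 × √1.296 = 13.3 (normal) or 11.86 × √1.296 = 13.5 (t).

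The range is therefore about 12.0 to 13.5. The Study site section counts 65 villages. If all contributed, m would be at most 88/65 = 1.35, DE at ICC 0.10 would be 1.035, and the result would be 11.9 (normal) or just under 12.1 (t).

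**Step 5: one area per arm, illustration only.** Put m = 39.6 into the same formula with assumed area-level ICCs (normal approximation):

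| Area ICC | DE | Detectable difference | Power for 12.5 |
|---|---|---|---|
| 0.01 | 1.386 | 13.8 | 72% |
| 0.02 | 1.772 | 15.6 | 61% |
| 0.05 | 2.930 | 20.0 | 42% |

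The slack found in step 3 is used up at an area ICC of (1.11 − 1)/38.6 to (1.14 − 1)/38.6, about 0.003 to 0.004.

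**Step 6: the plausibility sentence.** The target is a difference between groups. The support, +31.3 (25.6 to 37.0), is worded as a mean improvement after a training intervention. As worded, these are different quantities.

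**The case against.** **The error is small and conservative.** This stands for independent observations: the gap is 0.6 to 0.8 points, and power is 84% where 80% is claimed. The number recruited is set by the cohort, so the slip did not size the trial.

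**Village clustering may cost little.** This also stands. If participants are spread over all 65 villages, the slack in 12.5 covers the loss. It no longer does at 20 villages with ICC 0.05, where DE = 1 + 2.96 × 0.05 = 1.148.

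**The analysis may recover precision.** The Study design section provides a baseline assessment, and the Data management and analysis section provides general linear mixed models. With an assumed baseline correlation of 0.4 to 0.5, adjustment multiplies the detectable difference by √(1 − r²), which takes 11.9 to between 10.9 and 10.3. That is a fair sensitivity line, but the printed calculation does not use it, and no model separates area from treatment when each arm is one area.

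**The plausibility claim is mild.** If +31.3 were a before-after gain that recurred here, usual-care caregivers would have to gain 31.3 − 12.5 = 18.8 points before the contrast fell below 12.5. So 12.5 is not shown to be implausible. It is only not supported by this comparison alone.

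**Stronger readings that the document does not support.** A reader might infer that the Ghana figure came from an uncontrolled study. The cited study is not shown, so the point rests on the protocol's wording only. A reader might suppose that the 10% loss was taken off twice, or that the reference mean of 12.5 was copied into the result. Either is possible, but an SD near 19.9 would also give 12.5, and the text does not settle it. A reader might argue that the SD will be larger at follow-up, but the document gives no figure for that and does not say that the mean of 12.5 belongs to the caregivers who gained 31.3.

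**Conclusion.** The printed 12.5 is wrong for its own inputs: they give 11.7 (normal) to 11.9 (t), with about 84% power for 12.5. This rests only on stated figures and the usual two-sided convention.

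The missing cluster term carries more weight. Its size depends on assumed ICCs and village counts: about 12.0 to 13.5 for 20 to 40 villages at ICC 0.05 to 0.10, and under about 12.1 if all 65 villages contribute. The area-level figures of 13.8, 15.6 and 20.0 are illustrative. With one area per arm, the area effect is fully confounded with treatment, so a design-effect formula cannot give a valid detectable difference, and no individual-level claim of 80% power is assured.

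It would go too far to conclude that the trial is shown to be too small. The document does not establish that, and the arithmetic slip taken alone points the other way. What holds is that 80% power for 12.5 points is not a property of the stated inputs or of the allocation described. The paragraph should be corrected; the sample size need not change.

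**What to change.** Keep 88 children and rewrite the power paragraph:

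- State that with 39 to 40 analysed per arm, SD 18.6 and independent observations, the detectable difference at 80% power and two-sided 0.05 is about 11.9. If other inputs produced 12.5, print them.
- Add a sensitivity range labelled as resting on assumed ICCs: about 12.0 to 13.5 for village clustering (20 to 40 villages, ICC 0.05 to 0.10), and under about 12.1 if all 65 villages contribute. Replace the assumed village count with the actual one once it is known.
- Give 13.8, 15.6 and 20.0 for area-level ICCs of 0.01, 0.02 and 0.05 as illustration only. State that with one area per arm the area effect is confounded with treatment, so 80% power cannot be assured.
- Describe +31.3 as a mean improvement after training, and do not use it alone to justify the between-arm target. Cite a between-group estimate if one exists.

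The cost is one paragraph. No participants or procedures are added. The headline figure for independent data improves slightly, and the statement as a whole becomes less reassuring. The rewrite makes the confounding of area and treatment visible but does not remove it.
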